### Study population

140 children (6-12 years of age) and their caregiving custodial parents who experienced interparental violence will participate in this study.

### Inclusion and exclusion criteria

Children and their parents who experienced interparental violence and who are willing to take part in a secondary prevention program are eligible for participation in the study. Inclusion criteria to participate in the program and the study are: having experienced interparental violence, the violence has stopped at the time parent and child start with the program, and parent(s) has/have given informed consent to take part in the study. Exclusion criteria are: child/parent has such intellectual, psychiatric or behavioral problems that the behavior will impede functioning within the group and/or will create unsafety in the group for all participants.

### Procedure

In the Netherlands, parents and children who experience interparental violence are referred to a social service specialized in assisting families exposed to interparental violence in their neighbourhood (e.g. ASHG: Support Center for Domestic Violence, Women Shelters or Mental Health Care organizations) by police, other social services, youth care workers and health care professionals. These organizations offer, among other services, the intervention program. During the intake for the intervention program, all parents and children are informed that the organization offers two programs for children exposed to interparental violence in the study-period (intervention and control program) and they will be informed in which program they will participate as soon as possible. Information is provided about the study and every parent-child-dyad eligible for participation in the program is asked to participate in the study. If parent and child agree to participate in the study, they are asked to sign a consent form. If both parents have custody over the child, by Dutch law the other custodial parent needs to be informed about participation of his/her child in the study. The caregiving parent is asked to inform the other parent by means of an information brochure and letter from the researchers. In this letter the other parent is asked to give written consent for participation of the child in the study. Due to the law on privacy, the researchers are not allowed to contact the other parent directly. If no response of the other parent is received, and the caregiving parent has given written consent for participation, the child will be included in the study. This procedure has been established with the approval of the Medical Ethics Committee (METc VUmc 2009/99/NL26649.029.09), because of the specific problems in the family situation of the population participating in the study. If parent and child choose not to participate in the study, they can still enroll in the program.

Each group is randomly assigned to either the intervention or the control arm. Parents and children are given the details about the program into which they are randomized. Parents and children who participate in the study are invited to the setting (e.g. community centre, mental health clinic) at which the program (intervention or control) takes place one week before the program starts. They are asked to fill out questionnaires (T1). A week later the program starts for all parents and children. One week (T2) and six months (T3) after the end of the program parents and children who take part in the study are again invited to fill out questionnaires and participate in two observation tasks. If parents or children have trouble filling out the questionnaires, a trained masters student or an interpreter will assist. To check up on parents in the period between T2 and T3, parents are contacted by phone two times. Figure 1 shows the different stages of the research procedure and gives an overview of the instruments used at each assessment.

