### Randomization

An independent researcher will make the allocation schedule with a computerized random number generator. The random allocation list will be generated in blocks of no less than two, depending on the number of participating groups per time period. The numbers on the list will be paired with the groups in order of the date on which the groups start. The condition of the group will be disclosed to the participating organizations and to the researchers two weeks before the start of the program. Potential contamination of the intervention and control group will be avoided by restricting recruitment to one child per family.

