**Figure 1 F1:**
[figure not shown]
**Research procedure**. After informed consent is obtained, 2/3 of all parent-child dyads will be randomized into the experimental arm and 1/3 into the control arm. Parents and children are asked to fill out questionnaires (parent: TSCYC, CBCL, Questionnaire about duration and severity of domestic violence, demographic questionnaire, IES-R, HADS, PSI; child: CDI, TSCC, Questionnaire for children how to cope with difficult situations) at the first assessment (T1). A week later the program starts for all parents and children. One week (T2) and six months (T3) after the end of the program parents and children who take part in the study are again invited to fill out questionnaires and participate in two observation tasks (FIT and AEED). To check up on parents in the period between T2 and T3, parents are contacted by phone two times. At all assessments the teacher is also sent a questionnaire.

Parents receive €15,- after completing the first assessment, €25,- after participating in the program and completing the second assessment and €40,- after completing the follow up assessment. Children receive a gift after each assessment.

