### Interventions

#### Intervention program 'En nu ik...!' ('It's my turn now!')

The child sessions of the program 'En nu ik...!' are based on the psycho-educational secondary preventive intervention program 'Kids' Club' [20]. Changes in the original manual, with respect to topics and methods have been made. 'En nu ik...!' was further developed by including nine parallel group sessions for parents. Theoretical conceptualizations used in the development of this program are trauma theory [12] and attachment theory [18]. Child sessions of 'Kids' Club' have been adapted for use in the Netherlands by a consortium formed by the Women Shelter in Amsterdam (Blijf Groep), the Centre of Youth Care in Amsterdam (BJAA/SO&T), social work and mental health care services in Amsterdam (the Netherlands). The program consists of nine group sessions of 90 minutes each for children and nine parallel group sessions for their caregiving custodial parent. Each group has a maximum of eight children or parents. Usually a social worker together with a mental health care professional act as therapists. Therapists are trained in giving this standardized program and follow a protocol for every session. Therapists receive supervision during the program.

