#### Control program 'Jij hoort erbij' ('You belong')

For this study, an alternative control program was developed, based on a content analysis of nonspecific factors within the intervention program [23]. Basic elements of interventions, including positive attention from a therapist, positive expectations and hope, distraction and social support and recognition among group participants were deemed present in the intervention program, and were therefore built into the design of the control program as well; no specific attention is paid to the interparental violence. The reasons for the development of a control program were 1) to evaluate the need for specific factors in interventions, 2) to be able to monitor families in both arms equally well over time, and 3) to prevent higher drop-out rates in the control arm.

The control program follows the same structure as the intervention program and also consists of nine sessions of 90 minutes each for children and nine parallel group sessions for their caregiving custodial parent. The maximum group size is eight participants. Therapists are a clinical child psychologist/pedagogic specialist and a pedagogic specialist in training, for both parents and children. Therapists are trained in giving this standardized program and receive supervision during the program.

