### Sample size calculation

The total sample size is based on the expected differences in outcome measures between children participating in the secondary prevention program 'En nu ik...!' and the control program 'Jij hoort erbij'. Because the effect of the intervention program has been tested before in a non-experimental design [22], a conservative estimate of f = 0,25 [59] is made about the effect size. Based on an alpha of .05, a power of .80 in a two tailed test, 48 subjects in each condition are needed.

To answer the research questions concerning the influence of potential mediators and moderators on the effectiveness of the secondary prevention program, several multiple regression analyses with different predictors will be performed. Based on an alpha of .05, an expected medium effect size of f^2 ^= 0.15 and a N = 90 we will be able to achieve a power of .80 for a model with up to five predictors. In smaller models of up to two predictors it will also be possible to draw conclusions about the independent contribution of each predictor.

Because of the tumultuous time these families are in we expect a relatively high drop-out rate of around 45% from T1 to T3. For this reason, we aim to recruit 250 children and parents.

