### Data analyses

Most analyses will be done using the software program SPSS. Intention-to-treat and completer analyses will be performed. Descriptive analyses will be carried out by standard methods. The change in behavior will be assessed on a continuous scale, taking into consideration the scale of the different variables. For analyses of the primary outcome measures, we plan to use ANOVA repeated measure analyses and the scores of the children in the intervention group will be compared with their own scores on a previous assessment, as well as with scores of children in the control group at the same assessment. Mediator and moderator models will be tested, using data of all children (intervention and control group). Analyses and reporting of the results will be done according to the CONSORT 2010 Statement-guidelines [60].

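### Therapy groups are randomised, but the sample size and the repeated-measures ANOVA treat children as independent: for any positive within-group correlation the between-arm test exceeds 5%, and 48 per condition gives less than 80% power

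*Protocol article*

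**What the plan says.** **Unit of randomisation.** Procedure: "Each group is randomly assigned to either the intervention or the control arm". Randomization agrees: "The numbers on the list will be paired with the groups in order of the date on which the groups start", with block size depending on how many groups take part in a period. The Figure 1 legend is worded differently: "2/3 of all parent-child dyads will be randomized into the experimental arm and 1/3 into the control arm".

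**Group size.** For the intervention program, "Each group has a maximum of eight children or parents". For the control program, "The maximum group size is eight participants".

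**Sample size.** The inputs are an effect size ("a conservative estimate of f = 0,25 [59] is made about the effect size"), a two-sided alpha of .05 and a power of .80. The result is "48 subjects in each condition are needed". No ICC, design effect or number of groups appears. The recruitment target of 250 is explained by an expected dropout of about 45% from T1 to T3.

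**Analysis.** Data analyses: "For analyses of the primary outcome measures, we plan to use ANOVA repeated measure analyses". No therapy-group term is named, and clustering is not mentioned anywhere in the article.

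**The concern.** Children in one group share therapists, peers, setting, start date and a single allocation. The article itself counts social support among group participants as one of the nonspecific factors at work in both programs, so some similarity of outcome within a group is to be expected. A repeated-measures ANOVA accounts for occasions within a child. It does not account for children within a group. If the group is ignored, the between-arm comparison credits the trial with more independent information than it has.

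Two things follow. The test of each primary outcome rejects a true null hypothesis more often than 5% of the time, and the number needed per condition is too low for the stated power. The Trial objective section says that the results are meant to justify broad implementation, so a false positive would carry directly into that decision.

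**Working it through.** **Inputs from the article.** f = 0.25, which is d = 0.50 for two arms; two-sided alpha 0.05; power 0.80; 48 per condition (96 in total); groups of at most 8; dropout about 45%; 250 recruits.

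**Assumed inputs.** ICC of the analysed outcome 0.01 to 0.10, since none is given. Analysed children per group, m: 8 (full groups), 6 (partly filled), and 8 × 0.55 = 4.4 (completers from full groups).

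**Step 1: reproduce 48.** A plain two-sided t test at d = 0.50 needs 64 per arm, and at 48 per arm its power is 0.68, so that is not the source. A between-arm repeated-measures F test with two measurements and an assumed correlation of 0.5 needs 49 per arm; at 96 in total its power is 0.799. An ANCOVA with correlation 0.5 gives 48. In both, the variance is multiplied by 0.75: (1 + 0.5)/2 for the mean of two measurements, and 1 − 0.5² for the ANCOVA. The article states no correlation, so 0.5 is an inference. Each of these calculations treats children as independent (design effect 1).

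**Step 2: allow for the groups.**
- Design effect: DE = 1 + (m − 1) × ICC.
- True type I error of the test that ignores groups: 2 × [1 − Φ(1.96/√DE)].
- Number needed per arm: 48 × DE, rounded up. This leaves out the loss of degrees of freedom, so it is slightly favourable.
- Power at 48 per arm: noncentral t with noncentrality 0.5/√[0.75 × DE × (1/48 + 1/48)] and degrees of freedom equal to the number of groups minus 2.

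Worked example, m = 8, ICC 0.05: DE = 1 + 7 × 0.05 = 1.35; 1.96/√1.35 = 1.69, so the type I error is 9.2%; 48 × 1.35 = 64.8, so 65 per arm.

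| m | ICC | DE | True type I error | Needed per arm | Power at 48 per arm |
|---|---|---|---|---|---|
| 4.4 | 0.01 | 1.03 | 5.4% | 50 | 0.75 |
| 4.4 | 0.05 | 1.17 | 7.0% | 57 | 0.70 |
| 4.4 | 0.10 | 1.34 | 9.0% | 65 | 0.64 |
| 6 | 0.01 | 1.05 | 5.6% | 51 | 0.73 |
| 6 | 0.05 | 1.25 | 8.0% | 60 | 0.65 |
| 6 | 0.10 | 1.50 | 11.0% | 72 | 0.58 |
| 8 | 0.01 | 1.07 | 5.8% | 52 | 0.69 |
| 8 | 0.05 | 1.35 | 9.2% | 65 | 0.59 |
| 8 | 0.10 | 1.70 | 13.3% | 82 | 0.50 |

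Part of the power loss, and most of it at ICC 0.01, comes from testing on few groups (12 to 22) rather than from the design effect.

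**Step 3: simulation.** A t test that ignores groups was simulated under no effect, 20,000 trials per setting. With 6 v 6 groups of 8 it rejected in 9.0% (ICC 0.05) and 13.3% (ICC 0.10). With 16 v 8 groups of 6 it rejected in 7.4% and 11.0%. The formula holds up.

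**Step 4: the recruitment target.** 250 × 0.55 = 137.5, so about 137 completers against the 96 required. With 4.4 completers per group and a cluster-level test, power is 0.855 (ICC 0.05) and 0.805 (ICC 0.10) with equal arms. With the 2:1 split of the Figure 1 legend it is 0.81 and 0.76.

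**The case against.** Several points on the other side are fair.

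**The ICC is unknown and may be small.** At ICC 0.01 to 0.02 the type I error is only about 5.4% to 6.6%. This stands, and it makes the size conditional. The direction does not depend on it.

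**Eight is a ceiling.** Families who decline the study may still join the program, so a group may contain fewer than eight children with data. The 9% and 13% figures are therefore upper-end values for their ICCs. This stands. It is why 4.4 and 6 are shown as well.

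**The 250 recruits leave a cushion.** A reader might infer that the trial as a whole is underpowered. The article does not support that in general: Step 4 shows that power can stay near or above 80% at moderate ICCs. Nor should the eight-per-group design effect be applied to the 137 children left after dropout, because that pairs full groups with depleted numbers. The shortfall is shown for 48 per condition. The cushion is nevertheless presented as an allowance for dropout only, and it also requires that the 140 children named under Study population are not the number enrolled. If they were, 140 × 0.55 = 77 would remain, fewer than 96 before any clustering.

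**Moderator tests.** A reader might infer that every mediator and moderator test is inflated too. Most of the listed moderators vary between children within a group. A simulated interaction test with such a moderator that ignored groups, assuming a random group intercept only, rejected in 5.2% to 5.8%. General inflation of the moderator tests is not shown.

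**Change scores.** It could be argued that comparing change over time removes stable group differences. It does, but shared therapists and peers can also produce group-specific change, and that remains.

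**An unseen plan.** A separate analysis plan could add a multilevel model. The sample size and the primary analysis are, however, stated in this article, and both ignore the groups as written.

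**The Figure 1 legend.** Its wording may be shorthand for dyads allocated through their group. It describes no separate mechanism, so it needs reconciling but adds little to the case.

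**Conclusion.** The point holds as a unit-of-analysis error. Groups are randomised, while the sample size and the between-arm test are built on independent children. For any positive ICC the test exceeds its nominal 5%. Over an assumed ICC of 0.01 to 0.10 and 4.4 to 8 analysed children per group, the true level is about 5.4% to 13%: 7% to 9% at ICC 0.05 and 9% to 13% at ICC 0.10.

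On the basis that reproduces the article's own number, 48 per condition gives less than 80% power. With groups of 6 to 8, 60 to 65 per arm are needed at ICC 0.05 and 72 to 82 at ICC 0.10. The result rests on an ICC that the article does not give and on an inferred correlation of about 0.5 between measurements. The larger recruitment target may absorb part of the power loss, but a larger sample does not correct a standard error computed on the wrong unit.

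**What to change.** 1. State that the therapy group is the unit of randomisation, and reconcile the Figure 1 legend with the Randomization and Procedure sections.
2. Replace the repeated-measures ANOVA with a linear mixed model that has a random therapy-group effect, repeated occasions within child, and Satterthwaite or Kenward-Roger degrees of freedom.
3. Include the group effect in the mediator models and in any model that tests the arm effect or a group-level predictor.
4. Restate the power with 1 + (m − 1) × ICC over an ICC range of about 0.01 to 0.10, using the average number of analysed children per group and the intended allocation ratio.

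The cost is a less favourable stated power and somewhat more analysis work. Allocation is made by group, so membership should already be on record, and no extra participants or measurements are needed. The Status of the trial section says that data collection is still in progress, so the change can be made before results are known.

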**Methods/design:**

This study is a prospective multicenter randomized controlled trial across cities in the Netherlands. Participants (N = 140) are referred to the secondary preventive intervention program by police, social work, women shelters and youth (mental health) care. Children, aged 6-12 years, and their parents, who experienced interparental violence are randomly assigned to either the intervention program or the control program. The control program is comparable on nonspecific factors by offering positive attention, positive expectations, recreation, distraction, warmth and empathy of the therapist, and social support among group participants, in ways that are similar to the intervention program. Primary outcome measures are posttraumatic stress symptoms and emotional and behavioral problems of the child. Mediators tested are the ability to differentiate and express emotions, emotional security, coping strategies, feelings of guilt and parent-child interaction. Mental health of the parent, parenting stress, disturbances in parent-child attachment, duration and severity of the domestic violence and demographics are examined for their moderating effect. Data are collected one week before the program starts (T1), and one week (T2) and six months (T3) after finishing the program. Both intention-to-treat and completer analyses will be done.

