### Blinding

Parents, children, social workers as well as the researchers are blind to group allocation until two weeks before the start of the program. The condition is not disclosed earlier to avoid a bias in the intake procedure because of prior knowledge about the condition. Parents and children agree to participate in the study before randomization and without knowing in which arm they will be enrolled. Both programs are presented as useful programs by discussing the specific and/or nonspecific factors that can be of benefit to children and parents exposed to interparental violence. Every ID-number assigned to a parent-child-dyad is independent of the condition. The researchers coding the observation tasks and analyzing the data will be blind to the group condition of parents and children, as well as assessment (T1, T2, T3).

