##### Demographic variables

A demographic questionnaire is used to collect participant's demographic information. This questionnaire consists of 14 questions concerning ethnicity, living situation, education, social economic status and age and gender of the child.

All questionnaires for parents and children are combined in an attractive booklet. All instruments will be administered at all three assessment moments, with the exception of the demographic variables (only at T1) and part of the questionnaire about duration and severity of domestic violence (CTS2 and ACE only at T1), the interview about disturbed attachment behavior (only at T2) and the observation tasks FIT and AEED (not at T1).

Figure 1 provides an overview of the instruments used at each assessment.

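### The baseline assessment (T1) is scheduled after families can learn their arm, so parent and child baseline ratings may be affected and families who leave in between have no baseline

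*Protocol article*

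**What the plan says.** Consent comes before randomization, and whole groups are then allocated. The Blinding section states: "Parents, children, social workers as well as the researchers are blind to group allocation until two weeks before the start of the program". The Randomization section gives the same date for staff: "The condition of the group will be disclosed to the participating organizations and to the researchers two weeks before the start of the program". The Procedure section describes the group assignment, then says "Parents and children are given the details about the program into which they are randomized", and then describes the invitation to T1. The abstract and the Procedure section both place T1 one week before the program.

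T1 consists of parent and child questionnaires (Procedure; Figure 1 legend) and a form sent to the teacher. The two observation tasks, whose coders are blind, are not done at T1 (end of the section on demographic variables).

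The Drop-outs section follows all consenting families from randomization. It mails questionnaires to program drop-outs who cannot attend the post-test or follow-up, and applies last value carried forward if nothing comes back. The Data analyses section plans repeated-measures ANOVA, with intention-to-treat and completer analyses. The Sample size section expects about 45% drop-out between T1 and T3 and aims to recruit 250.

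**The concern.** Baseline is the one assessment at which families could still be blind. One arm receives the trauma-focused program, and the other a program that pays no specific attention to the violence. Families enter through the intake for the trauma-focused program, so they may react differently to the two announcements.

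Two things are at stake. First, the parent ratings (TSCYC, CBCL) and child self-reports (TSCC, CDI) at T1 enter the repeated-measures analysis, so a shift in T1 caused by knowing the arm would enter any contrast of change from T1. Second, a family may withdraw on hearing its arm. It would then have no baseline, and such losses could be unequal between arms. The protocol expected unequal loss in general: one stated reason for building the control program was to avoid higher drop-out in that arm.

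**Working it through.** **1. Time order.** Take the program start as week 0.
- Blinding of families, social workers and researchers ends: week −2 (Blinding; Randomization for organizations and researchers).
- Families are told their program: after group assignment and listed before T1 (Procedure). The exact day is not given.
- T1: week −1 (abstract; Procedure).

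T1 therefore falls about one week after blinding ends, and the order in the Procedure section agrees. No section holds disclosure back until T1 is complete.

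**2. Which T1 measures are exposed.** Parent and child questionnaires: yes. Teacher form: no section says that teachers learn the arm. Blind-coded observation: absent at T1, so the blinded coders give no protection there.

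**3. A family that leaves between disclosure and T1.**
- The mailing rule covers the post-test and follow-up, not T1.
- If the family never responds, there is no earlier value to carry forward.
- If it returns T2 or T3 by mail, a repeated-measures ANOVA with T1 as one of the occasions still drops it, because that analysis needs every occasion.

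**4. The drop-out allowance.** The plan's 250 is reproduced approximately by 140 / (1 − 0.45) = 254.5, or 255, which is within 3%; equally, 250 × 0.55 = 137.5. That 140 is the number wanted at T3 is an inference from this fit. Neither calculation has a term for loss between randomization and T1. Let w be that loss. The documents give no value, so 0 to 20% is assumed. The number at T3 is 250 × (1 − w) × 0.55, and the control arm is one third of it (2:1 allocation, Figure 1 legend). Recruitment that keeps 140 at T3 is 140 / [0.55 × (1 − w)].

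| w (assumed) | At T3 | Control arm | Recruitment for 140 at T3 |
|---|---|---|---|
| 0% | 137.5 | 45.8 | 255 |
| 5% | 130.6 | 43.5 | 268 |
| 10% | 123.8 | 41.3 | 283 |
| 20% | 110.0 | 36.7 | 319 |

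The control arm is already below the stated 48 at w = 0 because of the 2:1 split. Only the further fall down the column belongs to this point.

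**5. Size of a baseline shift (illustration).** The planned f = 0.25 corresponds to d = 2 × 0.25 = 0.5 for two equal groups. Suppose knowing the arm moves T1 in one arm by δ, and a share k of that shift persists to T2/T3.
- Change contrast: bias of size (1 − k) × δ. With k = 0 and δ = 0.1 to 0.2 SD, the bias is 0.1 to 0.2 SD; 0.1/0.5 = 20% and 0.2/0.5 = 40% of the planned effect. With k = 1 it is zero.
- T1 as covariate, k = 0, assumed correlation 0.6 and equal SDs: 0.6 × 0.1 = 0.06 SD to 0.6 × 0.2 = 0.12 SD.
- Arms compared at T2 or T3 alone, k = 0: the T1 shift does not enter.

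The values of δ, k and the correlation are all assumptions. The direction is unknown.

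**The case against.** The two-week date is deliberate: it protects the intake, and consent is given without knowledge of the arm. Both programs are presented to families as useful. The T1 instruments ask about fixed past periods (the past month for the TSCYC, the past two weeks for the CDI), which limits the room for a shift. The same respondents also know their arm at T2 and T3, so a lasting rating tendency would partly or wholly cancel in a change score. The plan also compares the arms at the same assessment, and a T1 shift does not touch that comparison at T2 or T3. All of this stands. It limits the likely size of the bias but leaves the order of events as it is.

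A reader might infer more than the documents support:
- *That families who withdraw on hearing their arm leave no data.* The Drop-outs section follows every consenting family from randomization and mails T2 and T3 questionnaires. What such a family lacks is a baseline.
- *That no intention-to-treat analysis could include them.* A likelihood-based mixed model or multiple imputation could use T2 and T3 without T1. The limit applies to the planned repeated-measures ANOVA and to carrying values forward.
- *That such losses would go unseen.* Reasons for drop-out are to be documented and analyzed, and reporting follows CONSORT 2010.
- *That the whole baseline is unblinded, including its administration.* Teachers are not said to know the arm. The researchers are told at week −2, but T1 is filled in by the families; whether the students or interpreters who help some of them know the arm is not stated.

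**Conclusion.** The concern holds in a limited form. On the protocol's own dates, T1 follows the point at which families can learn their arm, so the parent- and child-reported baseline is open to influence from that knowledge. A family lost between disclosure and T1 has no baseline, drops out of the planned repeated-measures ANOVA, and is not covered by the 45% allowance.

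This rests on the order of events in the Procedure section, since the exact day on which families are told is not given. The size is not known. The 20 to 40% of d = 0.5 is an illustration for a shift of 0.1 to 0.2 SD that does not persist; any persistence reduces it for a change contrast. The documents do not show that a bias occurs or which way it would go. The change is worth making because it is cheap and protects the only assessment that can be blind.

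**What to change.** Complete T1 before the condition is disclosed to families and to anyone who assists them at T1. There are two ways:
- Keep the two-week notice for the organizations, and tell families only after they have handed in T1. This costs families about one week of notice, in a setting where the protocol promises to inform them as soon as possible, and organization staff must withhold the arm for that week.
- Move T1 to just before disclosure. The baseline then lies one to two weeks earlier, with a longer gap to the program.

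Either way, a family that attends T1 and then withdraws on hearing its arm has a baseline. Inclusion was already under way when the article was written, so the change would apply to the remaining groups through an amendment to the ethics committee, a route that the protocol provides. For groups already run, report by arm the losses between consent or randomization, disclosure and T1. This needs only counts from records of families who are in any case followed from randomization.
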